### Assignment of interventions: blinding

#### Who will be blinded {17a}

This is an observational cohort study with no therapeutic or clinical interventions assigned; therefore, blinding of participants or care providers is not applicable.

However, to minimize bias and ensure objective analysis:Outcome Assessors (AI Developers/Data Scientists):The data analysis team at Maulana Azad National Institute of Technology (MANIT), Bhopal, responsible for developing and evaluating the AI prediction models, will be blinded to the identity of individual participants and their school affiliations. Only anonymized and coded datasets will be used for model training and validation.Field Investigators and Clinical Examiners:Field personnel conducting ocular examinations and data collection at schools will be unaware of which participants will be included in the longitudinal follow-up phase at the time of initial data collection. This is to prevent any differential treatment or attention.Participants:As no clinical intervention is administered and participants are not exposed to comparative groups, blinding of participants is not relevant.

This level of blinding is appropriate to the study design and ensures that both data collection and analysis are conducted with minimal risk of observational or analytical bias.

### Procedure for unblinding if needed {17b}

As this is a non-interventional, observational cohort study, no participants or care providers are blinded to a treatment assignment. Consequently, there is no formal “allocation” to be unblinded and the standard unblinding procedures for clinical trials do not apply.

However, in the context of our data-analysis blinding—whereby the AI development team at MANIT works exclusively with anonymized, coded data—the following applies:Circumstances permitting re-identification (unblinding):Safety concerns: If an unexpected ocular finding during data analysis suggests an urgent need for clinical follow-up (e.g., detection of a sight-threatening condition), the coding key may be accessed by the Principal Investigator to identify and refer the participant for immediate care.Data verification or audit: For regulatory or ethical audits, the Sponsor or Ethics Committee may request linkage between coded data and participant identity to confirm compliance or investigate reported issues.Procedure for revealing participant identity:Authorization: Any request to access the coding key must be approved in writing by the Principal Investigator ([name]) and the Institutional Ethics Committee of AIIMS Bhopal.Controlled Access: A designated data-management officer will retrieve the minimal necessary identifiers and provide them only to the clinical team for the stated purpose.Documentation: All unblinding events will be logged in the trial master file, including date, reason, personnel involved, and actions taken.

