#### Data security and storage

Data will be stored on a secure, password-protected institutional server with access restricted to authorized personnel only.Regular automated daily backups will be performed to ensure data redundancy.Access to the identifiable dataset (e.g., name, school, contact) will be strictly limited to the Principal Investigator and designated data managers for follow-up coordination.All field devices (e.g., tablets or laptops) used for data collection will be encrypted and configured to auto-wipe in case of a security breach.

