#### Storage and protection

Electronic data will be stored on secure, password-protected servers managed by the research IT team at MANIT Bhopal.Identifiable information will be stored separately from de-identified clinical and questionnaire data.Access to identifiable data will be restricted to the Principal Investigator, data managers, and follow-up coordination team.

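### Urgent re-identification of a child, read literally, waits for two written approvals, including one from the ethics committee

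*Protocol article*

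**What the plan says.** Item 17b of the protocol article (Procedure for unblinding if needed) deals with breaking the code that separates the analysis team from the children's identities. It gives two grounds.

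- **Safety.** If an unexpected ocular finding in the data points to an urgent clinical need, "the coding key may be accessed by the Principal Investigator to identify and refer the participant for immediate care".
- **Audit or verification.** Here "the Sponsor or Ethics Committee may request linkage between coded data and participant identity".

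One procedure follows, in three steps, with no separate branch for either ground.

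- **Authorization:** "Any request to access the coding key must be approved in writing by the Principal Investigator" "and the Institutional Ethics Committee of AIIMS Bhopal".
- **Controlled access:** "A designated data-management officer will retrieve the minimal necessary identifiers and provide them only to the clinical team for the stated purpose".
- **Documentation:** "All unblinding events will be logged in the trial master file, including date, reason, personnel involved, and actions taken".

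Two other sections bear on who can see identities. Under Data security and storage, access to the identifiable dataset "will be strictly limited to the Principal Investigator and designated data managers for follow-up coordination". Under Storage and protection: "Access to identifiable data will be restricted to the Principal Investigator, data managers, and follow-up coordination team".

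**The concern.** The safety ground exists so that a child can be referred immediately. The Authorization step applies to every request and joins the two approvers with *and*, so both must sign before the key is opened. An ethics committee does not normally decide within the hour, and the article sets no deadline for this decision. A rule written to protect privacy could therefore hold up the clinical referral that the same section is meant to allow.

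At stake is the timeliness of care for a child with a suspected sight-threatening condition. No endpoint, sample size, error rate or estimate depends on it.

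**Working it through.** The article gives no figure to reproduce, so the check is a close reading of the text, plus one count.

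**1. Does the Authorization step cover the urgent ground?** Its wording is universal. The Controlled access step points the same way: it releases identifiers to the clinical team and to nobody else. That suits referral of a child. It does not suit the audit ground, where the sponsor or the ethics committee asks for the linkage. The three steps are therefore hard to read as audit-only.

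**2. Is one approval enough?** No. The sentence names the principal investigator and the ethics committee jointly.

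**3. Is there an exemption, retrospective approval or time limit?** None appears in item 17b or elsewhere in the article. By contrast, the adverse event sections do set limits: serious events are reported to the ethics committee within 24 h and reviewed by the safety subcommittee within 48 h.

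**4. Does another section waive the step?**

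| Section | What it offers | Does it waive the approvals? |
|---|---|---|
| Data security and storage; Storage and protection | Standing access to identifiable data for the principal investigator and data managers | No. Neither mentions the coding key, and identifiers are kept apart from the de-identified clinical data |
| Implementation (16c) | The field team contacts children selected for follow-up, with no committee step stated | No. It covers scheduling of follow-up visits |
| Provisions for post-trial care (30) | Referral of any child found to have an undiagnosed condition | No. It does not say how a coded record is linked to a child |
| Assessment of outcomes (18a) | On-site examination, with a senior clinician re-checking inconsistencies | No. Item 17b deals with what on-site examination missed |
| Coordinating centre and steering committee (5d) | A clinical panel reviews flagged measurements, biannually or once a substantial batch has built up | No. Its schedule is not an urgent one |

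**5. How many children depend on this route?** From Sample size (14), about 5,000 children are examined at baseline and about 500 are followed.

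- Children with no scheduled visit after baseline: 5,000 − 500 = 4,500.
- Share: 4,500 / 5,000 = 90%.

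For these children, a finding missed on site has no later study examination at which to be caught. This is the number without a second look. It is not the number expected to have an urgent finding, which the article does not give.

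**6. How long is the delay?** It cannot be calculated, because no committee turnaround time is stated. The Participant timeline (13) puts baseline examinations in months 2–9 and training of the first model in months 9–12. A finding first noticed during that training would then be between 9 − 9 = 0 and 12 − 2 = 10 months old. Data cleaning starts in month 6 and could reveal it sooner. Any wait for approval is added to that interval.

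**The case against.** The strongest reply is that the conflict comes from choosing the stricter reading. The safety ground speaks of the principal investigator *accessing* the key, and only the audit ground speaks of a *request*. Since the Authorization step governs requests, it may be aimed at other parties who apply to the principal investigator. On the strict reading, principal investigators would have to approve their own access in writing, which is odd. This reading is open. The release of identifiers to the clinical team alone counts against it, and the article does not choose between the two. Staff should not have to settle the question in an emergency.

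Second, the data-handling SOPs in the internal Data Management Plan, which are not shown, may contain an urgent route. That is possible. The complaint, however, is about a rule the article states in universal terms and not about detail it left out.

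Third, a working link from code to identity must already exist, because about 500 selected children are contacted as routine. Together with standing access to identifiable data, on-site examination and direct referral, this makes harm unlikely. That stands, and it is why the point is minor.

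Fourth, prior committee approval before re-identifying minors is a legitimate safeguard, and the study treats children as a vulnerable population. This also stands. It is a reason to keep joint approval where time allows, as it does for audits.

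**Conclusion.** The point holds as a minor one. Item 17b permits access for immediate care and then sets out a single procedure that, taken literally, makes such access wait for two written approvals with no urgent route and no deadline. A delay is possible, not certain. Its length and frequency cannot be estimated from the article, and urgent findings first seen in coded data should be rare.

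The conclusion assumes that the three-step procedure applies to both grounds and that no internal SOP overrides it. If the SOPs already let the principal investigator act alone in urgent cases, all that is needed is to bring the published sentence into line with them. The statistical analysis is unaffected either way.

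**What to change.** Amend the Authorization sentence in item 17b so that the two grounds are handled differently.

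- **Urgent safety concern:** the principal investigator alone may authorise access to the coding key at once. The event goes into the trial master file log that the section already requires. The ethics committee is notified promptly afterwards, for example within the 24 h already used for serious adverse event reports. That limit is borrowed from another process, and the committee may prefer a different one.
- **Audit or data verification:** keep prior written approval by both the principal investigator and the ethics committee.

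The cost is a one-sentence amendment approved by the ethics committee. The log already exists, so no staff or new procedures are needed. The price is that the committee would review rare urgent re-identifications of minors after the event instead of before it.

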## Data collection and management

### Plans for assessment and collection of outcomes {18a}

#### Baseline and follow-up data collection

Data will be collected in two phases: a cross-sectional baseline assessment (Phase 1) and a longitudinal follow-up (Phase 2). Data collection will be performed on-site in schools across the Bhopal division (Madhya Pradesh, India) by trained field teams from AIIMS Bhopal.Demographic and lifestyle data (questionnaire-based):Instruments: Structured, pre-tested questionnaires administered to parents/guardians and students (as age-appropriate)Variables collected: Age, gender, dietary habits, screen time, near work duration, outdoor activity, family history of myopia, socio-economic statusReliability/Validity: Based on instruments used in previously validated school eye health studies (e.g., AIIMS Delhi NIM Study); pre-tested in a local pilot survey.Ocular assessments (clinical examination):Performed using portable, validated ophthalmic instruments by optometrists and ophthalmologists:Uncorrected Visual Acuity (UCVA) and Best Corrected Visual Acuity (BCVA): Standard Snellen chartCycloplegic Auto-refraction: Handheld autorefractometer with keratometry (validated device)Axial Length and Corneal Thickness: Portable A-scan with pachymeterCorneal Curvature and Refraction Power: Recorded during auto-refractionFundus Photography: Non-mydriatic portable fundus camera

All measurements will be conducted in duplicate where applicable (e.g., axial length) to ensure reliability, and any inconsistencies will be re-checked by a senior clinician on-site.

#### Follow-up assessments (every 6 months for 24 months)

Participants selected for longitudinal follow-up will undergo the same clinical and questionnaire-based assessments at each 6-month interval. Changes in spherical equivalent refraction and axial length will be primary outcome measures.

### Data quality assurance measures

Training and standardization: All examiners will undergo centralized training by AIIMS Bhopal prior to field deployment; SOPs will be strictly followedInter-observer calibration: Random sample reviews will be performed to assess inter-observer variability and maintain consistencyReal-time data entry: Digital data entry using custom forms in a secure, encrypted platform with built-in range and consistency checksDaily field verification: On-site supervisors will verify 5% of randomly selected entries each dayData backup and auditing**:** Data will be backed up daily and subject to weekly audits by the data coordination team at MANIT

#### Data collection forms

Detailed Case Report Forms (CRFs) and questionnaires are available as supplementary materials to this protocol and have been submitted to the Institutional Ethics Committee. Electronic CRFs are programmed into the data capture platform to minimize manual errors.

### Plans to promote participant retention and complete follow-up {18b}

To minimize attrition and ensure high follow-up rates during the 24-month longitudinal phase, the following measures will be implemented:School and parent engagement:oOngoing collaboration with school principals and parent–teacher associations to maintain institutional support.oEducational sessions and feedback to parents regarding their child’s eye health to foster trust and continued participation.Communication and reminders:oSMS and phone call reminders to parents prior to each follow-up visit.oDistribution of appointment cards at each visit, with the next scheduled date printed clearly.Flexible scheduling and on-site visits:oFollow-up assessments will be planned during school hours at convenient times to avoid academic disruption.oRe-visits scheduled for absentees to ensure maximum data recovery.Minimal invasiveness and incentives:oAll assessments are non-invasive, encouraging cooperation.oAge-appropriate educational materials or certificates of participation will be provided as positive reinforcement.

#### Data collection for participants lost to follow-up

For participants who discontinue participation in the longitudinal follow-up:Last Available Ocular Data (e.g., visual acuity, axial length, spherical power) and baseline demographics will be retained for analysis.Reasons for discontinuation (e.g., transfer to another school, withdrawal of consent) will be documented.Wherever feasible, a final assessment will be attempted before exit, with parental consent.

Missing data will be addressed during statistical analysis using appropriate imputation techniques where required, as described in the statistical analysis plan.

### Data management {19}

#### Data entry and coding

All data will be entered digitally at the point of collection using encrypted electronic case report forms (eCRFs) developed in collaboration with the data science team at MANIT Bhopal.Each participant will be assigned a unique anonymized identification** code** to maintain confidentiality.**Range and logic checks** will be built into the data entry interface to flag missing, out-of-range, or inconsistent responses in real-time. For select critical variables (e.g., axial length, visual acuity), duplicate entry and verification will be performed to minimize transcription errors.

#### Data security and storage

Data will be stored on a secure, password-protected institutional server with access restricted to authorized personnel only.Regular automated daily backups will be performed to ensure data redundancy.Access to the identifiable dataset (e.g., name, school, contact) will be strictly limited to the Principal Investigator and designated data managers for follow-up coordination.All field devices (e.g., tablets or laptops) used for data collection will be encrypted and configured to auto-wipe in case of a security breach.

#### Quality assurance procedures

A data monitoring committee comprising members from AIIMS Bhopal and MANIT will conduct monthly audits of 5–10% of data entries.A data dictionary and standard operating procedures (SOPs) for data handling have been developed and shared with all data collection teams.Discrepancies or missing values identified during audit will be queried and resolved within 5 business days.

#### Location of detailed procedures

The complete Data Management Plan (DMP), including SOPs for data handling, coding structure, and version control protocols, is maintained as an internal document and is available upon request from the Principal Investigator.

### Confidentiality {27}

All personal information of participants—including names, contact details, school identifiers, and medical data—will be collected, stored, and managed in strict accordance with ethical standards and institutional data protection protocols to ensure confidentiality before, during, and after the study.

#### Collection and handling

Identifiable data (e.g., name, school, phone number) will be collected only once at enrolment, solely for the purpose of informed consent, participant tracking, and follow-up coordination.Each participant will be assigned a unique study ID code, which will be used throughout the data collection and analysis process to ensure pseudonymization.All physical documents (e.g., signed consent forms) will be stored in locked cabinets at AIIMS Bhopal, accessible only to authorized study personnel.

#### Storage and protection

Electronic data will be stored on secure, password-protected servers managed by the research IT team at MANIT Bhopal.Identifiable information will be stored separately from de-identified clinical and questionnaire data.Access to identifiable data will be restricted to the Principal Investigator, data managers, and follow-up coordination team.

#### Sharing and dissemination

Only de-identified, aggregate-level data will be used for publication, presentation, or model training.Any data shared with collaborators or third-party academic institutions will be governed by data sharing agreements and will exclude personally identifiable information.

#### Post-trial confidentiality

All identifiable data will be retained for a period of 10 years post-trial in secure archives, after which it will be disposed of in accordance with institutional and national data retention policies.Participants will be informed of these procedures during the consent process.

### Summary of data flow

Data will be collected at school sites using electronic case report forms, encrypted and transmitted to a secure central server. Following cleaning and validation, de-identified datasets will be processed by the MANIT data science team for feature engineering, model training, and cross-validation. The best-performing model will then be integrated into a mobile application for field-level deployment, where predictions will be generated using real-time input data without altering standard clinical care.

These measures are designed to uphold the principles of confidentiality and data integrity as outlined in the ICMR Ethical Guidelines (2017) and GDPR-aligned best practices for data protection in research.

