### Objectives {7}

#### Primary objective

To develop and validate an artificial intelligence (AI)-based predictive model for assessing myopia progression among school-going children aged 6–18 years, based on demographic, environmental, and ocular health parameters.

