#### Secondary objectives

To systematically collect and analyse cross-sectional and longitudinal data on myopia-related risk factors in children from diverse socio-economic backgrounds in urban and rural areas of the Bhopal division.To identify and rank key predictors (e.g., axial length, screen time, parental myopia) contributing to myopia progression using machine learning algorithms.To design and deploy a mobile application embedded with the AI model to facilitate field-level risk prediction and early screening without the need for specialist intervention.To conduct awareness programs aimed at the prevention and early intervention for myopia progression in school children. 

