## Interventions

This is a non-interventional, observational cohort study; therefore, no clinical or therapeutic intervention will be administered to participants as part of the trial.

The “intervention” in this study pertains to the development and application of an artificial intelligence (AI)-based predictive model for myopia progression, which will utilize data collected through non-invasive, standard ophthalmic assessments and structured questionnaires. All procedures are observational and diagnostic in nature and include:Visual acuity testing (unaided and best-corrected)Cycloplegic auto-refractionAxial length and corneal thickness measurementsFundus photographyLifestyle and demographic data collection (screen time, outdoor activity, dietary habits, parental myopia history, etc.)

These procedures will be conducted by trained ophthalmologists and optometrists using validated, portable instruments. No drugs, therapeutic regimens, or experimental clinical procedures will be introduced as part of this study.

The AI model and associated mobile application will be applied to collected data retrospectively and prospectively for prediction purposes only, without influencing or altering standard clinical care pathways for participants.

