### Plans for collection, laboratory evaluation and storage of biological specimens for genetic or molecular analysis in this trial/future use {33}

This study does not involve the collection, storage, or laboratory evaluation of biological specimens for genetic or molecular analysis. All data collected will be observational, comprising non-invasive ocular measurements, demographic information, and behavioral risk factors related to myopia progression.

Accordingly:No biological samples (e.g., blood, saliva, or tissue) will be obtained from participants.No laboratory-based genetic or molecular testing is planned as part of the current study protocol or any ancillary study.All predictive analyses will rely solely on imaging (e.g., fundus photography) and structured clinical and environmental datasets.

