## Statistical methods

### Statistical methods for primary and secondary outcomes {20a}

#### Primary outcome analysis

Objective: To quantify and predict myopia progression over time based on spherical equivalent refraction (SER) and axial length measurements.Approach:oDescriptive statistics (mean, standard deviation) will be used to report baseline characteristics.oLinear mixed-effects models will be applied to assess longitudinal changes in SER and axial length over follow-up periods, accounting for repeated measures and potential confounders (e.g., age, screen time, parental myopia).oTime-to-event analysis (e.g., Kaplan–Meier estimates) may be used to assess time to clinically significant myopic progression (e.g., ≥ –0.50 D/year), if applicable.

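### Nothing planned would show that the app predicts myopia progression without a specialist

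*Protocol article*

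**What the plan says.** **Purpose of the app.** The Secondary objectives ask for an app giving "field-level risk prediction and early screening without the need for specialist intervention".

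**Model in the app.** The Summary of data flow says: "The best-performing model will then be integrated into a mobile application for field-level deployment". Section {6b} on comparators says the algorithms are compared to find the most accurate one.

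**Inputs.** The Primary objective describes a model "based on demographic, environmental, and ocular health parameters". The Secondary objectives list "key predictors (e.g., axial length, screen time, parental myopia") as examples to be ranked. Section {33} adds: "All predictive analyses will rely solely on imaging (e.g., fundus photography) and structured clinical and environmental datasets".

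**Who collects the inputs.** The Interventions section lists acuity, cycloplegic autorefraction, axial length and corneal thickness, fundus photography and questionnaire items, and states: "These procedures will be conducted by trained ophthalmologists and optometrists using validated, portable instruments". Section {18a} names a handheld autorefractor, a portable A-scan with pachymeter and a fundus camera, again used by optometrists and ophthalmologists.

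**How the app is judged.** Under Secondary outcomes in {12}, app predictions are compared with clinical diagnoses by positive predictive value, together with ease-of-use ratings, at a pilot at 18 months. Under {20a}, agreement with clinician-confirmed cases is measured by Cohen's kappa. The timeline in {13} puts the pilot in months 30–36 and the last visit at month 36.

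**How the model is judged.** Under Primary outcome in {12}, AUROC, sensitivity and specificity are evaluated against change in refraction and axial length.

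**The concern.** The objective combines two claims: that the tool predicts risk of progression, and that it does so without a specialist. The route to the app serves neither claim directly. Choosing on accuracy alone from a set that includes biometry and imaging favours a model that needs those measurements. The app's own endpoints then compare its output with a clinical diagnosis, which need not say anything about later change.

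The Secondary outcomes section says the app outcome will determine whether a school-level screening tool is viable, and the Abstract expects the app to inform national screening strategies. A favourable kappa could then be read as support for specialist-free prediction of progression, although no planned analysis examined it.

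**Working it through.** No sample-size or power formula applies. The check compares sections and then does the timeline arithmetic.

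**1. Inputs against the objective**
- Required by the Secondary objectives: use without a specialist.
- Selection rule in {6b} and the Summary of data flow: highest accuracy. Whether an input can be obtained in the field is not a stated criterion.
- Candidate inputs in the Primary objective, {18a} and {33}: questionnaire items and acuity, plus cycloplegic refraction, axial length, corneal measures and fundus images. Ophthalmologists and optometrists take the ocular measurements.
- Not found anywhere: a model limited to inputs a non-specialist can collect, or a pilot in which non-specialists obtain the inputs.

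**2. Reference standard against the objective**
- Model level, {12} Primary outcome: change in refraction and axial length, which is progression.
- App level, {12} Secondary outcomes and {20a}: clinical diagnoses and clinician-confirmed cases. Neither is defined as progression after the prediction was made.

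**3. Timeline**

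The plan's figure is reproduced first. Phase 2 follows month 12, so the visits at months 18, 24, 30 and 36 fall at 6, 12, 18 and 24 months of follow-up. A pilot at 18 months is 12 + 18 = month 30, which matches the start of the months 30–36 window. The two statements of pilot timing agree.

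Follow-up left after a pilot prediction = 36 − month of prediction:
- month 30: 36 − 30 = 6 months
- month 33: 36 − 33 = 3 months
- month 36: 36 − 36 = 0 months

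Section {20a} analyses "time to clinically significant myopic progression", with 0.50 D per year as its example. The robustness checks in {20b} add 1.00 D per year. To observe a full horizon after pilot predictions:
- 12 months: 30 + 12 = month 42 to 36 + 12 = month 48
- 24 months: 30 + 24 = month 54 to 36 + 24 = month 60

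Both lie beyond the last visit at month 36.

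**4. What the planned data would allow instead**

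Observation to month 36 if the app's model is run on inputs already collected:
- baseline (months 2–9): 36 − 9 = 27 to 36 − 2 = 34 months
- month 18 visit: 36 − 18 = 18 months
- month 24 visit: 36 − 24 = 12 months

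Each window is at least one year. The data for a proper check will therefore exist, but the plan does not specify this check for the app.

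**The case against.** **The model is tested against progression.** The app only carries a model, and {12} evaluates that model against change in refraction and axial length, using cross-validation folds and independent test sets. The Interventions section also allows retrospective as well as prospective application. This stands. A reader might infer that the trial cannot show prediction of progression at all, and the documents do not support that. These provisions do not, however, test prediction from inputs a non-specialist could collect.

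**The reference may not be present myopia.** A reader might take the app to be scored against current diagnoses only. The documents do not say so: a case is undefined, and the adjudication panel in {5d} verifies progression status as well as myopia. That is a fair limit. On either reading, at most 6 months of change can follow a pilot prediction.

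**Inputs are not final.** The Summary of data flow speaks only of real-time input, and model selection criteria are assigned to an analysis plan not shown. Not needing a specialist could also mean not needing one to interpret the result, and optometrists with portable devices may not count as specialists. Dependence on specialist measurements is therefore a strong inference, not a stated fact. The mismatch between an accuracy-only choice and the stated use remains in the protocol text.

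**Screening is half of the objective.** Positive predictive value and kappa against diagnosis suit early screening. This stands, and is why those measures should be kept and labelled as detection.

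**The size of any inflated agreement is unknown.** It is tempting to say kappa will be near-perfect because the cohort is half myopic. No calculation supports that, and no section says in whom the pilot is run.

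**Conclusion.** The point holds as a gap in what is planned: no analysis would show that the app predicts progression without a specialist. The app's model is chosen without regard to who can collect its inputs, its endpoints are not tied to later progression, and its pilot leaves 0 to 6 months of follow-up against thresholds stated per year.

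This rests on two assumptions. The most accurate model is taken to draw on the specialist-collected measurements, which is probable but not stated. The app's reference case is taken to be something other than progression observed after the prediction, because neither app endpoint names progression.

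The conclusion does not extend to the full-input model, whose prediction of progression can be assessed as planned. Nor does it follow that a weaker model must go into the app; that is a design trade-off for the investigators. The matter concerns a secondary outcome of a study described as exploratory, but the remedy is cheap and lets the study answer its own objective.

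**What to change.** 1. Pre-specify an additional model limited to inputs a non-specialist can collect, list those inputs, and report its performance beside the full-input model. Age, unaided acuity and questionnaire items are one possible set; the choice is the investigators'.
2. Score whichever model the app carries on baseline and earlier-visit inputs (months 18 and 24) against progression observed to month 36, in children not used for training. The model is to be refined after every follow-up round, so these children should be set aside before refinement starts, or predictions should be strictly out-of-fold.
3. Define the reference case for the app. Report positive predictive value and kappa against clinical diagnosis separately, as a detection measure.
4. If the app carries the full-input model, reword the secondary objective so that it does not assert specialist-free prediction.

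**Cost.** One more model fit and one scoring run on data already being collected, with no added visits. The restricted model will probably perform less well than the full one; the documents give no figure for the loss. Setting children aside reduces the training data, which out-of-fold scoring largely avoids.
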